## Abstract

**Background:**

Post‐stroke cognitive impairment (PSCI) is a common complication following stroke, with limited effective treatments. This randomized controlled trial aims to evaluate the efficacy of two non‐pharmacological interventions—electroacupuncture therapy (EA) and herbal olfactory therapy (HOT)—in improving cognitive function in PSCI patients, both as standalone treatments and in combination.

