**Methods:**

This parallel‐group, assessor‐blinded, randomized controlled trial will recruit 210 PSCI patients, randomly assigned to one of six groups: control, EA, HOT, combination therapy, sham therapy, or the healthy (ratio 1:1:1:1:1:1). All participants will receive standard cognitive training and basic medical care. The EA group will receive 4 weeks of electro‐acupuncture at specific acupoints. The HOT group will receive 4 weeks of aromatic inhalation therapy using Acorus tatarinowii volatile oil. The combination group will receive both interventions. The primary outcome measure is cognitive function, assessed using the Montreal cognitive assessment (MoCA) at baseline, week 4, and week 8. Secondary outcomes include the mini‐mental state examination (MMSE), functional magnetic resonance imaging (fMRI), near‐infrared spectroscopy (fNIRS), and anxiety assessment using the state‐trait anxiety inventory (STAI) at baseline and week 4. Data analysis will be conducted using a modified intention‐to‐treat approach.

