**FIGURE 1 brb370631-fig-0001:**
[figure not shown]
Flow diagram of the study.

The sample size for this study will be calculated using the formula for a superiority trial of two independent sample sizes. Clinical experience and preliminary research indicated an effective rate of 90% in the treatment group and 80% in the control group (Hei et al. 2023, Su et al. 2023, Zhang et al. 2023). Based on these data, we conducted a sample size calculation using a two‐tailed *t*‐test with the following parameters: test boundary value *δ* = 0.15, significance level *α* = 0.025, and power *β* = 0.20 (Zabor et al. 2020). The calculation was performed using the following formula.

$$n=\left[{\left(Z_{\alpha /2}+Z\beta \right)}^{\wedge 2}*\left(p1\left(1-p1\right)+p2\left(1-p2\right)\right)\right]/{\left(\delta -|p1-p2|\right)}^{\wedge 2}$$

Considering a case number ratio of k = 1 between groups, the calculated sample size was 32 cases per group. To account for a potential 10% dropout rate, we increased the sample size to approximately 35 cases per group (International Council for Harmonisation of Technical Requirements for Pharmaceuticals for Human Use 1998). The total sample will be divided into 6 groups: control, EA, HOT, combination therapy, sham therapy, or the healthy, totaling around 210 cases to be included.

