### Data Analysis

2.11

Researchers who are blind to the groupings will conduct data management and statistical analysis on the data acquired using the statistical software SPSS 22.0 (SPSS Inc., Chicago, IL, United States). Descriptive statistics will be utilized to depict the baseline characteristics of the two participant groups, with mean ± standard deviation for normally distributed continuous data and median and quartiles for non‐normally distributed continuous data. The normality of the data will be assessed using the Shapiro–Wilk test, and the homogeneity of variance will be assessed using the Levene test. One‐way analysis of variance (ANOVA) will be used for comparisons among multiple groups for normally distributed continuous data, while repeated measures analysis of variance will be used for within‐group pre‐ and post‐treatment comparisons. The Kruskal–Wallis test will be employed for non‐normally distributed continuous data. The significance level (α) for the statistical hypothesis tests will be set at *p* < 0.05, one‐tailed.

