## Discussion

3

PSCI is a form of cognitive dysfunction that can occur following a stroke. Two non‐pharmacological treatment methods that have gained attention for their minimal side effects are traditional Chinese medicine olfactory inhalation therapy and electric neck acupuncture. Electric acupuncture has been widely used in treating neurological conditions like cerebral ischemia, Alzheimer's disease, and Parkinson's disease (Cai et al. 2019, Shin et al. 2017, Kong et al. 2010). Electric neck acupuncture, a novel technique developed by [name], leverages the anatomical, physiological, and pathological features of the neck to treat neurological disorders effectively (Liu et al. 2017). While there is limited research on the efficacy of electric neck acupuncture for PSCI, TCM olfactory inhalation therapy focuses on enhancing cognitive function and emotional well‐being by stimulating the olfactory nerve in brain regions associated with the sense of smell. Ancient texts like the Divine Farmer's Materia Medica mention the therapeutic benefits of olfactory inhalation therapy for conditions such as senile dementia, stroke, and epilepsy. HOT works through the aroma molecules of plants, which are transmitted to the limbic system of the brain and even through the pores of the human body, penetrating into the deeper tissues, resulting in muscle relaxation and a pleasant emotional feeling. Studies have shown that the use of calamus volatile oil by gavage for three weeks can reduce nitric oxide synthase (NOS) in the brain and hippocampus of Alzheimer's disease mouse models, and significantly improve learning and memory dysfunction (Tian et al. 2012). Inhalation of eugenol over a 4‐week period enhanced learning memory by interfering with neurotransmitters in the olfactory system, thereby altering olfactory afferent signals (Shuai et al. 2021). Our study aims to explore the potential of traditional Chinese medicine olfactory inhalation therapy and electric neck acupuncture, either individually or in combination, as treatments for PSCI.

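### The unadjusted one-way ANOVA in section 2.11 ignores baseline MoCA and does not itself estimate the combination and standalone effects the trial asks about

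*Protocol article*

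**What the plan says.** **Analysis (section 2.11).** Between groups, one-way "analysis of variance (ANOVA) will be used for comparisons among multiple groups for normally distributed continuous data"; Kruskal–Wallis is the alternative for non-normal data. Repeated-measures ANOVA is named only for change within groups. No covariate, contrast or interaction is mentioned. The significance level is 0.05, one-tailed.

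**Questions.** The Abstract (Background) sets out to evaluate EA and HOT "both as standalone treatments and in combination". The Discussion repeats this: "either individually or in combination, as treatments for PSCI". The Abstract (Aims) puts the specific focus on whether the combination is superior to the monotherapies.

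**Arms.** By label, four of the six groups are control, EA, HOT and both. Section 2.6.4 gives the combination group the procedures of 2.6.2 and 2.6.3. The other two groups are sham and healthy; section 2.4 describes the healthy group as a separate cohort serving the imaging comparison.

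**Background treatment.** The Abstract (Methods) says: "All participants will receive standard cognitive training and basic medical care". Section 2.6.1 calls the control group the standard drug treatment group and describes donepezil there. Sections 2.6.2 to 2.6.4 do not say whether EA, HOT or combination patients receive it.

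**The concern.** The primary outcome, MoCA, is a score measured at baseline, week 4 and week 8. A one-way test on the groups gives a single verdict that some group differs from some other. It does not say by how much the combination differs from EA or from HOT, which is the stated focus. The section does not say which groups enter the test. If the healthy group is included, the test could reject simply because healthy people score higher than patients. A one-tailed level also has a clear meaning only for a directed contrast, not for an F test over several groups.

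Baseline MoCA is collected but not used in the between-group comparison. Precision is lost, and chance baseline imbalance, which is quite possible with 35 per arm, carries through to the result.

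At stake is whether the trial reports prespecified estimates of the effects it was set up to measure, or a global p-value followed by comparisons chosen after seeing the data.

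**Working it through.** **1. The plan's own number (section 2.1).** Inputs: "an effective rate of 90% in the treatment group and 80% in the control group"; "test boundary value *δ* = 0.15"; "significance level *α* = 0.025"; "power *β* = 0.20". The variance term is 0.9×0.1 + 0.8×0.2 = 0.25.

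- With z = 1.960 and denominator (0.15 + 0.10)²: (1.960 + 0.842)² × 0.25 / 0.0625 = 31.4, so 32. This reproduces the stated figure.
- The formula as printed has denominator (0.15 − 0.10)² = 0.0025. It gives 785 with z = 1.960, or 951 with z for α/2 = 0.0125.

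That discrepancy is a separate matter. Here 32 is taken as the planned evaluable number per arm and 35 as the enrolled number. The sizing rests on response rates and the article gives no MoCA difference or SD, so everything below is in SD units with assumed effect sizes.

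**2. Standard errors, 32 per arm, common SD, no baseline adjustment.**

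- Two-arm comparison: √(2/32) = 0.250
- Factorial main effect (64 vs 64): √(2/64) = 0.177
- EA-by-HOT interaction: √(4/32) = 0.354

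**3. Power at one-tailed 0.05.** Power = Φ(d/SE − 1.645). For d = 0.5:

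- two-arm: Φ(2.000 − 1.645) = 64%
- main effect: Φ(2.828 − 1.645) = 88%
- interaction of that size: Φ(1.414 − 1.645) = 41%

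| Assumed effect (SD) | Two-arm | Main effect, additive | Interaction of that size |
|---|---|---|---|
| 0.3 | 33% | 52% | 21% |
| 0.4 | 48% | 73% | 30% |
| 0.5 | 64% | 88% | 41% |
| 0.6 | 77% | 96% | 52% |

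The effect detectable with 80% power is (1.645 + 0.842) × SE: 0.62, 0.44 and 0.88 SD respectively.

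**4. If the effects are not additive.** Take 35 per arm and an EA effect of 0.5 SD without HOT. The two-arm SE is √(2/35) = 0.239, so power is 67%. The main-effect SE is √(1/35) = 0.169.

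- Effect unchanged with HOT: main effect 0.5, power 91%.
- Effect halved with HOT: main effect (0.5 + 0.25)/2 = 0.375, power 72%.
- Effect absent with HOT: main effect (0.5 + 0)/2 = 0.25, power 43%.

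**5. If only control receives a drug with effect D.** Let EA and HOT each have effect 0.5 and add without interaction, with D = 0.3. Arm means are control 0.3, EA 0.5, HOT 0.5, combination 1.0.

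- EA main effect: [(0.5 + 1.0) − (0.3 + 0.5)]/2 = 0.35, a bias of −D/2.
- Interaction: 1.0 − 0.5 − 0.5 + 0.3 = 0.30, a bias of +D.
- EA vs control: 0.5 − 0.3 = 0.2, which is EA against the drug.
- Combination vs EA: 1.0 − 0.5 = 0.5, unaffected.

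**6. Baseline adjustment.** With correlation r between baseline and follow-up MoCA, the SE of a contrast shrinks by about √(1 − r²) relative to an unadjusted comparison of follow-up scores. The article gives no r, so no figure is put on this gain.

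**The case against.** The strongest reply has three parts.

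*The plan is not wrong, only brief.* A one-way ANOVA on four arms and a two-way model with interaction fit the same arm means, so every contrast proposed here can be drawn from either. Naming contrasts is often left to an analysis plan, which is not at hand. This stands in part: missing contrasts alone would be no finding. But the article does fix the between-group method for its primary outcome. That method, as stated, is unadjusted and does not itself produce the estimates the aims call for.

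*The design is not shown to be factorial.* A reader might infer that the four arms are a clean 2×2 crossing, that each standalone effect should therefore rest on 70 vs 70, and that the plan throws away half its information. The documents do not support this. The article never calls the design factorial. Section 2.6.1 makes control the donepezil group, and the other arms' sections are silent, so a cell receiving neither treatment on a common background is not established. The objection stands on this point.

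*Standalone means alone.* EA without HOT is properly estimated by EA vs control. A main effect averages over the presence and absence of HOT and equals the standalone effect only without interaction. With 41% power for a 0.5 SD interaction, the test could not reliably warn against pooling. Nor does pooling help combination vs each monotherapy, which keeps its two-arm SE. This also stands, and is why main effects are kept in a supporting role.

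**Conclusion.** The point holds in this limited form. The between-group analysis in section 2.11 leaves out baseline MoCA and does not itself estimate combination vs EA, combination vs HOT, or either therapy alone. The lead contrasts can be specified now: they do not involve the control arm, so the donepezil question does not touch them provided EA, HOT and combination share a background.

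The factorial summaries are conditional. With 32 evaluable per arm, a common background and additive effects, the SE falls from 0.250 to 0.177 SD, and power for an assumed 0.5 SD effect rises from 64% to 88%. Interaction can reverse that gain, and a drug given only to controls biases the main effects by −D/2 and the interaction by +D. Effect sizes are assumptions throughout, because the article gives no MoCA difference or SD.

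**What to change.** In section 2.11, replace the between-group analysis of MoCA with one linear model on the control, EA, HOT and combination arms, adjusted for baseline MoCA, leaving out the sham and healthy groups. From it report, with confidence intervals:

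1. combination vs EA and combination vs HOT, as the main contrasts;
2. EA vs control and HOT vs control, for the standalone questions.

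Separately, reconcile the Abstract with sections 2.6.1 to 2.6.4 on which arms receive donepezil. Until that is done, the meaning of the contrasts against control is also unclear. If background treatment proves common to all four arms, and only then, add the EA-by-HOT interaction with its confidence interval and the two factorial main effects as supporting estimates. The interaction test should not decide whether the other results are reported.

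The cost is analysis wording: same patients, same measurements, same software. The downside is slightly more analysis, and main effects that must be read beside the simple effects because they mislead if the therapies interact.

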**Aims:**

This study aims to evaluate the clinical efficacy of EA at cervical acupoints combined with HOT for PSCI, with a specific focus on determining the therapeutic superiority of this combined approach over monotherapy interventions.

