Modern pharmacological studies have shown that ATR can protect central neurons, enhance memory and learning functions, resist nerve cell apoptosis, and inhibit central cholinergic activity, leading to significant therapeutic effects (Wang et al. 2023, Xu et al. 2023). Herbal olfactory therapy (HOT) using traditional Chinese medicinal materials triggers biochemical reactions in the respiratory, nervous, and circulatory systems, influencing human emotions, physiology, and behavior (Zhang et al. 2021). The volatile oil of ATR can quickly penetrate the blood‐brain barrier to provide therapeutic benefits. Moreover, certain acupuncture points have been found to stimulate brain activity and cognitive function. For example, Suliao (GV25) is known for its ability to clear heat and improve mental clarity, while Yingxiang (LI20) can enhance energy flow and cognitive function. By applying essential oils to these specific acupoints, the absorption of the oils can be enhanced, leading to improved therapeutic outcomes.

Electroacupuncture therapy (EA) involves connecting an electroacupuncture device to acupoints in the neck area and has been used in the clinical treatment of cerebral ischemia with significant therapeutic effects. [name] proposed a novel treatment method for cerebrovascular diseases, which includes needling the bilateral Fengchi (GB20) and Gongxue to stimulate them with pulsed electric currents (Liu et al. 2017). This stimulation improves inadequate cerebral blood supply and enhances cerebral blood circulation. Electroacupuncture connecting the Fengchi (GB20) and Gongxue has shown noticeable effects in promoting meridian function, regulating metabolism, and improving limb and language functions in patients with head and neck diseases such as brainstem ischemia (Fu et al. 2023, Wang et al. 2009). This study aims to evaluate the clinical efficacy of electroacupuncture combined with ATR volatile oil inhalation therapy in treating PSCI. The research seeks to provide evidence that the integration of EA with ATR volatile oil inhalation therapy offers superior clinical benefits compared to single‐modality treatments for PSCI, through rigorous clinical investigation.

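### The aim is superiority of the combination over each monotherapy, but the stated tests are omnibus or within-group and address neither contrast

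*Protocol article*

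**What the plan says.** The Aims paragraph of the Abstract describes the trial as "with a specific focus on determining the therapeutic superiority of this combined approach over monotherapy interventions". The Introduction repeats this: the evidence sought is that EA with the volatile oil "offers superior clinical benefits compared to single"-modality treatment.

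Section 2.11 (Data Analysis) assigns tests by purpose:
- Between groups: one-way ANOVA "will be used for comparisons among multiple groups for normally distributed continuous data", and the Kruskal–Wallis "test will be employed for non"-normal data.
- Within groups: "repeated measures analysis of variance will be used for within"-group comparison before and after treatment.
- Significance: 0.05, one-tailed, for the hypothesis tests generally.

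The same section speaks of "the baseline characteristics of the two participant groups", although sections 2.1 and 2.4 list six groups, five of patients and one healthy. Section 2.1 sizes a single two-sample comparison, with an "effective rate of 90% in the treatment group and 80% in the control group", and calls it two-tailed with alpha 0.025. The primary outcome (section 2.7.1) is MoCA at weeks 0, 4 and 8.

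**The concern.** The null hypothesis of the one-way ANOVA is that all group means are equal. Rejecting it says that some difference exists somewhere, not that the combination beats EA or HOT. A pre/post test compares no arms at all. Followed as written, the plan can finish without testing its headline question.

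The one-tailed level does not repair this. With more than two groups, an F or Kruskal–Wallis test responds to differences in any direction, so a one-tailed level cannot express superiority of one named arm. The level also differs from the one in the sample-size section.

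What is at stake is the main conclusion. A significant ANOVA driven by a low control or sham arm could be reported as support for the combination when it adds nothing to either monotherapy.

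**Working it through.** **Inputs.** The planned number after dropout, 32 per group, is from section 2.1. Effects are in SD units and are my assumption, because the article gives no MoCA SD or target difference.

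**The plan's own figure.** The printed formula does not return 32. With the stated inputs it gives (2.241 + 0.842)² × (0.09 + 0.16) / (0.15 − 0.10)² ≈ 951 per group, or 785 with z = 1.960. That is a separate matter. I take 32 as the planned number.

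**1. Omnibus test when the combination adds nothing.** Put control and sham at 0, and EA, HOT and combination all at e. The grand mean is 0.6e, so the sum of squared deviations is 3(0.4e)² + 2(0.6e)² = 1.2e². The noncentrality is λ = 32 × 1.2e² = 38.4e², with 4 and 155 degrees of freedom and level 0.05.

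| e (SD) | λ | P(reject) |
|---|---|---|
| 0.2 | 1.54 | 14% |
| 0.3 | 3.46 | 27% |
| 0.5 | 9.60 | 68% |
| 0.7 | 18.82 | 95% |
| 0.8 | 24.58 | 99% |

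If sham behaves like the active arms, the sum is 0.8e² and λ = 25.6e². The test then rejects 19%, 49% and 81% of the time at 0.3, 0.5 and 0.7 SD.

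**2. If the healthy group enters the ANOVA.** Put all five patient arms at 0 and healthy at 1 SD. The sum of squared deviations is 5(1/6)² + (5/6)² = 0.833, so λ = 26.7 with 5 and 186 degrees of freedom. The test rejects about 99% of the time with no treatment difference of any kind.

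**3. Significance levels.** One-tailed 0.05 uses a critical z of 1.645, two-tailed 0.05 uses 1.960, and two-tailed 0.025 uses 2.241. Sections 2.11 and 2.1 therefore set different bars.

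**4. The two contrasts that match the aim.** They share the combination arm, so with equal arms their correlation is 0.5. With n = 32 the standard error is √(2/32) = 0.25 SD. If the combination exceeds each monotherapy by δ, let c = 4δ − z. The power to win both is Φ₂(c, c; 0.5), and for one contrast it is Φ(c).

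| δ (SD) | One contrast, two-sided 0.05 | Both, two-sided 0.05 | Both, two-sided 0.025 |
|---|---|---|---|
| 0.3 | 22% | 10% | 6% |
| 0.5 | 52% | 35% | 24% |
| 0.71 | 81% | 70% | 59% |
| 0.8 | 89% | 82% | 73% |

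For 80% joint power at two-sided 0.05, the arms would need 218, 79 and 31 patients at 0.3, 0.5 and 0.8 SD.

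**5. Error under two decision rules, one visit, one-sided 0.05, combination equal to both.** If either contrast may be claimed alone, the error is 1 − Φ₂(1.645, 1.645; 0.5) = 0.088. If both must win, it is Φ₂(−1.645, −1.645; 0.5) = 0.012, rising to at most 0.05 when one monotherapy is clearly inferior.

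**The case against.** Four points on the other side deserve weight.

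- **Follow-up comparisons may be specified elsewhere.** Post hoc tests and adjustments are commonly left to an analysis plan or full protocol, which is not shown here. That is right. A reader might infer that every pairwise comparison will be run unadjusted at one-tailed 0.05 with no error control. The article does not support this: it describes no pairwise tests, no family of pairs, and no rule allowing a claim on whichever arm or visit succeeds. If both contrasts must win, no adjustment is needed. The point rests on the tests and level that are stated.
- **The rejection rates depend on the assumptions.** They do. They run from 14% to 99% over 0.2 to 0.8 SD, and no single value should be quoted as the size of the problem. Control receives donepezil (section 2.6.1), so a large gain over it is a strong assumption. The sham arm's content is also unclear, since section 2.6.6 points to 2.6.5, which describes olfactory treatment while citing 2.6.1.
- **Such a rejection is not a false positive.** The arms do differ in that scenario. The harm arises only when the result is read as an answer to the stated aim.
- **The article has other aims.** The Abstract background and the Discussion also ask about EA and HOT individually, and an among-group test bears on those. It still does not serve the specific focus.

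The reference to two groups concerns baseline description only and is a minor slip.

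**Conclusion.** The mismatch stands. The stated aim needs combination versus EA and combination versus HOT. The stated between-group tests address neither, the within-group tests compare no arms, and one-tailed 0.05 has no meaning for an omnibus test and disagrees with section 2.1.

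The consequence depends on effect sizes that the article does not give. At 32 per arm, with control and sham alike, the omnibus test rejects in about a quarter to almost all trials (27% at 0.3 SD, 95% at 0.7 SD) when the combination adds nothing. Including the healthy group would make rejection nearly certain at a 1 SD gap, but section 2.11 does not say whether it is included.

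On error rates the supported statement is narrow. If either contrast could be claimed alone at one-sided 0.05, the error at one visit would be about 9%. Larger inflation figures would need decision rules that the article never states.

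**What to change.** In section 2.11:

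1. Make the primary analysis two prespecified contrasts on MoCA, combination minus EA and combination minus HOT, at one named visit. Week 4 or week 8 is the sponsor's choice.
2. Restrict it to the randomised patient arms and exclude the healthy group.
3. Claim superiority over monotherapy only if both contrasts are significant in favour of the combination, at one two-sided alpha that is the same in sections 2.1 and 2.11. No split of alpha is needed.
4. Treat the omnibus test, the within-group tests and all other pairs as secondary.
5. Correct the reference to two groups.
6. State joint power over a range of assumed MoCA differences.

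No arm, visit or treatment changes, so the text itself costs little. The real cost is what the power statement will show: winning both contrasts is harder than winning one (70% against 81% at 0.71 SD, two-sided 0.05). At 32 per arm, joint power is only about 35% at 0.5 SD and 10% at 0.3 SD, and lower still if the common alpha is two-sided 0.025. Unless a difference near 0.8 SD over each monotherapy is credible, the sponsor would have to enlarge the arms or present the comparison as exploratory.

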#### Primary Outcomes

2.7.1

Participants' cognitive abilities will be assessed at three‐time points: baseline (week 0), during treatment (week 4), and follow‐up (week 8) (Table 2). The primary outcome measures include the Montreal Cognitive Assessment (MoCA), which are commonly used tools for evaluating cognitive function across different types of impairment.

**TABLE 2 brb370631-tbl-0002:** Schedule of enrollment, intervention, and assessment.

	Week 0 (baseline)	Week 4	Week 8
MMSE	X	X	X
MoCA	X	X	X
MBI	X	X	X
TCD	X	X	
fNIRS	X	X	
fMRI	X	X	
STAI	X	X	
Adverse Effects			

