### Safety Monitoring

2.9

Acupuncture and olfactory therapy pose mild adverse effects. Acupuncture may cause pain, numbness, or bruising, while olfactory therapy may lead to allergic reactions or affect the liver or kidneys. Serious adverse events will be promptly reported, and patients experiencing such events will be withdrawn from the study. Adverse events will be documented on case report forms and reported to statisticians.

Adverse events (AEs) are typically classified into three severity grades: mild, moderate, and severe. Mild adverse events refer to symptoms that are tolerable to participants, requiring no specific intervention, and do not affect the trial progression or participant prognosis. Moderate adverse events involve clinically significant symptoms that are difficult for participants to tolerate, potentially necessitating trial discontinuation or medical treatment, and may impact disease recovery. Severe adverse events are life‐threatening conditions that could lead to permanent disability or mortality, requiring immediate trial termination and emergency medical intervention. During the treatment period, any adverse events must be documented in real‐time, investigated for causality, and promptly reported to the supervising physician for evaluation and management.

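### No baseline-adjusted between-arm test of MoCA is specified: arms are compared by one-way ANOVA or Kruskal–Wallis without a covariate, and repeated measures ANOVA is confined to within-group change

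*Protocol article*

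**What the plan says.** The Aims paragraph of the protocol article's abstract sets a between-arm question: "determining the therapeutic superiority of this combined approach over monotherapy interventions". The Methods paragraph of the abstract says that the primary outcome, cognitive function, is "assessed using the Montreal cognitive assessment (MoCA) at baseline, week 4, and week 8". Table 2 puts MMSE and MBI on the same three visits, and STAI, TCD, fNIRS and fMRI at weeks 0 and 4 only.

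Section 2.11 (Data Analysis) gives each method a task:

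- One-way ANOVA "will be used for comparisons among multiple groups for normally distributed continuous data".
- Kruskal–Wallis takes its place for non-normal continuous data.
- For the repeated visits, "repeated measures analysis of variance will be used for" comparing scores before and after treatment within each group.

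The section names no covariate and no group-by-time term. It does not say whether the ANOVA response is the week 4 score, the week 8 score or the change from baseline. It sets the tests at 0.05, one-tailed.

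**The concern.** Two things do not fit the aim.

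First, the only method that is given the repeated measurements looks inside each arm. In this trial a within-arm gain has several causes besides the treatment under test. The abstract (Methods) and section 2.6.1 give cognitive training to every patient. Section 2.2 admits patients below MMSE cut-offs, which invites regression to the mean, and 3–6 months after stroke, when recovery may still be under way. The scales are also repeated, so practice can raise scores. A significant gain in the combination arm beside a non-significant one in a monotherapy arm is not evidence that the arms differ.

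Second, neither between-arm method, as assigned, takes the baseline score as a covariate. The trial plans about 32 evaluable patients per arm, and baseline adjustment is a source of precision that needs no extra patient or visit.

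**Working it through.** **Inputs from the article.** Planned evaluable number: 32 per arm (section 2.1). With 35 recruited and 10% dropout, 35 × 0.9 = 31.5, which agrees. I take 32 as given; how the sample-size formula leads to it is a separate question.

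**Assumptions.** The article gives no SD for MoCA and no baseline-to-follow-up correlation r. Effects are therefore in SD units, and r is taken as 0.3, 0.5 and 0.7. The main figures use two-sided 0.05 and the normal approximation.

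**Error variance relative to a raw week score.** Raw score: 1. Change score: 2(1 − r). ANCOVA: 1 − r².

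**Unadjusted comparison of two arms.** SE = √(2/32) = 0.25 SD. Detectable difference at 80% power = (1.96 + 0.84) × 0.25 = 0.70 SD. Power for 0.5 SD = Φ(0.5/0.25 − 1.96) = Φ(0.04) = 51.6%.

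**Adjusted comparison.** The SE is multiplied by √(1 − r²), so power for 0.5 SD = Φ(2/√(1 − r²) − 1.96).

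| r | ANCOVA variance | Reduction | Detectable difference | Power for 0.5 SD | Change-score variance | Change-score ÷ ANCOVA variance |
|---|---|---|---|---|---|---|
| 0.3 | 0.91 | 9% | 0.67 SD | 55.4% | 1.40 | 1.54 |
| 0.5 | 0.75 | 25% | 0.61 SD | 63.7% | 1.00 | 1.33 |
| 0.7 | 0.51 | 51% | 0.50 SD | 80.0% | 0.60 | 1.18 |

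A t-based calculation is slightly lower: 50% unadjusted, 62% at r = 0.5 and 79% at r = 0.7.

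The last column is 2(1 − r)/(1 − r²) = 2/(1 + r). If the ANOVA is run on change scores, ANCOVA is still worth about 1.2 to 1.3 times the sample at r = 0.5–0.7. A change score is less precise than the raw week score when r is below 0.5.

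**At the plan's one-tailed 0.05.** Replace 1.96 by 1.645. The unadjusted detectable difference is (1.645 + 0.84) × 0.25 = 0.62 SD, falling to 0.54 (r = 0.5) or 0.44 (r = 0.7). Power for 0.5 SD is Φ(0.355) = 64% unadjusted, against Φ(0.664) = 75% at r = 0.5 and Φ(1.156) = 88% at r = 0.7.

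**Within-arm tests used as a comparison.** Suppose two arms have the same true change and each within-arm test has power p. The chance that exactly one is significant is 2p(1 − p): 50% at p = 0.5 and 32% at p = 0.8. A non-specific gain of 0.5 SD of change is enough for p of about 78% at n = 32 (two-sided paired t), or 87% one-sided.

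**The case against.** The strongest defence is that an unadjusted comparison of randomised arms is valid and unbiased, so this is a matter of efficiency and not an error. That stands. The article also nowhere says that within-arm gains will be read as efficacy; its aim is worded as a comparison. That stands too, but section 2.11 then names no test of between-arm change to serve that aim.

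A reader might infer more than the article supports:

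- *That change is never compared between arms and the baseline score is wasted.* The ANOVA response is not stated. It could be change from baseline, which uses the baseline and compares change. What can be said is that no such test is specified; the table shows that ANCOVA is more precise than either reading at each r considered.
- *That incomplete patients are deleted, against the modified intention-to-treat analysis announced in the abstract ("Data analysis will be conducted using a modified" intention-to-treat approach).* No section says so. It would be an inference from how classical repeated measures ANOVA is usually run, and that analysis is the within-group one. A one-way ANOVA at a visit loses only patients without that visit. Missing-data rules and the definition of the analysis set may sit in a full protocol or analysis plan that is not shown. Section 2.9 says that "patients experiencing such events will be withdrawn from the study", but gives no expected number and does not show that scores are discarded.
- *That a chance baseline imbalance passes in full into the result.* With raw follow-up scores only r times the imbalance carries over. One SE of imbalance (0.25 SD) shifts the estimate by 0.075, 0.125 or 0.175 SD at r = 0.3, 0.5 or 0.7.

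It is also fair to object that the gain depends on an assumed r. At r = 0.3 it is small: power rises from about 52% to 55%.

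**Conclusion.** The point holds as one of analysis choice and should be acted on. Section 2.11 assigns the between-arm question to methods without a baseline covariate and limits the repeated-measures method to within-group use. It therefore specifies neither a baseline-adjusted between-arm test of MoCA nor an arm-by-time test, although the aim is a between-arm contrast.

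The planned between-arm test is valid; what is lost is precision. Depending on r, which the article does not give, the loss runs from slight (r = 0.3) to about half the error variance (r = 0.7) if raw scores are compared, and is smaller at the higher correlations if change scores are compared. The second weakness does not depend on r: within-arm significance cannot establish superiority of the combination over either monotherapy.

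**What to change.** For MoCA, and likewise MMSE and MBI, state in section 2.11 that the efficacy test is a between-arm comparison among the five PSCI arms, adjusted for the baseline score of the same scale. Leave out the healthy cohort, which section 2.4 includes as a normal reference for brain function. Either of two forms will do:

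- ANCOVA at one primary week, week 4 or week 8, which the sponsor names in advance; or
- a mixed model on weeks 4 and 8 with arm, visit, arm-by-visit and baseline-by-visit, using all available post-baseline scores.

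Name combination versus EA and combination versus HOT as the key contrasts. For continuous outcomes measured only at weeks 0 and 4, use ANCOVA with the baseline value. Report within-arm change as descriptive only.

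The cost is a change of analysis wording. It needs no new data, visit or patient, and no change in the follow-up of patients who leave the study.
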